In parallel with the system feasibility and usability study, we plan to develop and psychometrically test a set of remote balance and functional mobility tests delivered via the telerehabilitation system (WP3). We will adapt and manualize 5 remote mobility tests that are collected through the telerehabilitation system: the 30-second sit-to-stand (30STS) test, timed-up-and-go (TUG) test, functional reach test (FRT), 20-second single-leg stance (20SLS) test, and the Short Physical Performance Battery (SPPB). The SPPB includes the following tests: side-by-side stand (10 seconds), semitandem stand (10 seconds), tandem stand (10 seconds), a gait speed test over 3 meters, and a 5-time repeated chair stand test. Upon completion of the developmental phase, we will conduct a test-retest reliability study for in-person and telehealth data capture and a criterion validity study comparing telehealth and in-person data with 15 people with MS (EDSS 2.5-6.5) at each site (n=60).

To examine the efficacy of the advanced telerehabilitation solution for people with MS, we propose an international feasibility multicenter RCT (WP4). We will include a target sample of 24 participants per country (in 4 countries; 96 participants in total) based on the stepped rule of thumb proposed by Whitehead et al [33], who estimated the optimal sample size for an early-stage/pilot RCT to be 24. Importantly, as the results may differ across countries, we consider each country an individual site for the feasibility RCT. Statistical analysis will be performed for the total group and each country separately. The participants will be randomly allocated (individual randomization) into one of two groups: (1) home-based telerehabilitation exercise training via the WizeCare platform [28] or (2) usual care. The sample criteria for the feasibility multicenter RCT will be the same as those for WP2.

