### Outcome Measures for the Feasibility Multicenter RCT

The outcome measures for WP4 will include the 30STS [36] (primary outcome), SPPB [37], 6-minute walk test (6MWT) [38], timed 25-foot walk test (T25FWT) [39], mini-BESTest (balance) [40], FRT [41], and a self-report questionnaire, the 12-item MS Walking Scale (MSWS-12) [42]. In accordance with the project’s secondary aims, we will examine the impact of the intervention programs on mood (ie, depression and anxiety with the State-Trait Anxiety Inventory [STAI] [43] and Quick Inventory of Depression Symptomology [QIDS] [44]), quality of life (EQ-5D-5L [45]) and the impact of MS (29-question Multiple Sclerosis Impact Scale; MSIS-29 [46]).

All outcome measures will be collected at baseline (at the initiation of the intervention program), and after the intervention period’s completion. Assessors (physical therapists) will be blinded to group allocation, and patient report outcomes will be collected using an online form. Other significant disease-related factors collected solely at baseline (together with demographic and relevant clinical information) will include perceived fatigue (Modified Fatigue Impact Scale; MFIS [47]) and cognition (Symbol Digit Modality Test; SDMT [48]). Additionally, we will collect baseline information on digital literacy, which may confound the intervention’s effectiveness. All outcome measures used for the study have been validated in people with MS and are recommended for rehabilitation and clinical trials.

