### Data Analysis and Statistical Plan

Each research question is addressed through specific outcome measures. For RQ1, usability and feasibility will be assessed via the TUQ, adherence rates, dropout rates, and stakeholder interviews, with qualitative data analyzed thematically. RQ2 involves psychometric evaluation of remote assessments (e.g., SPPB, STS, and TUG) using intraclass correlation coefficients for test-retest reliability and Pearson correlations to compare remote and in-person scores. RQ3 and RQ4 outcomes (eg, 30STS, MSWS-12, EQ-5D-5L, STAI, and QIDS) will be analyzed using linear mixed models to assess within- and between-group effects over time. The primary analysis will follow an intention-to-treat principle, including all randomized participants in the groups to which they were originally assigned, regardless of adherence to the intervention protocol. A per-protocol analysis may be conducted as a secondary exploratory analysis. Missing data will be addressed using multiple imputation, assuming data are missing at random, and sensitivity analyses will be performed to assess the robustness of results.

As part of RQ5, the study also incorporates a comprehensive economic evaluation of the telerehabilitation system, which complements the clinical analyses and addresses a critical gap in MS rehabilitation research. A cost-utility analysis will be conducted to compare the telerehabilitation intervention and usual care, using incremental cost-effectiveness ratios derived from health care service use data and EQ-5D-5L–based quality-adjusted life years. Cost data will include implementation, infrastructure, maintenance, training, support services, and any differences in health service use or patient-reported outcomes. These data will be collected alongside the RCT to ensure alignment between clinical effectiveness and economic impact.

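### With two visits, the mixed-model analysis should state a baseline-adjusted contrast between arms; its conventional form is an unbiased but less precise change-score comparison

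*Protocol article*

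**What the plan says.** All statements are in the Protocol article.

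- **Model** (Data Analysis and Statistical Plan): outcomes for research questions 3 and 4 "will be analyzed using linear mixed models to assess within- and between-group effects over time". Fixed effects, treatment of the baseline score and covariates are not named.
- **Visits** (Outcome Measures for the Feasibility Multicenter RCT): "All outcome measures will be collected at baseline (at the initiation of the intervention program), and after the intervention period’s completion". That makes two time points.
- **Main efficacy measure** (same section): "The outcome measures for WP4 will include the 30STS [36] (primary outcome").
- **Size and allocation** (Methodology, Approach, and Study Population): "We will include a target sample of 24 participants per country (in 4 countries; 96 participants in total"), with a pilot rule of thumb as the basis. On allocation: "The participants will be randomly allocated (individual randomization) into one of two groups".
- **Country** (same section): "Statistical analysis will be performed for the total group and each country separately".

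**The concern.** In a randomised trial any difference between arms at baseline is due to chance. A model that gives each arm its own baseline mean estimates that difference anyway. With two visits its group-by-time term then subtracts the whole chance imbalance from the follow-up difference, although only the part predicted by the correlation between visits should be removed. The result is a wider interval than the same data could give.

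The trial has 96 participants, and analyses of 24 are planned within each country. The Discussion says the results should inform the design of a fully powered trial, so the precision of the 30STS estimate has a use beyond this study. The baseline scores that would recover the lost precision are already being collected.

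**Working it through.** **The plan's own figure.** 24 participants × 4 countries = 96, as stated. It comes from a rule of thumb, so there is no effect size, SD, alpha or power to recompute.

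**Inputs.** From the article: two visits, 96 participants, two arms. Assumed, because the article gives no value: 1:1 allocation (48 per arm), outcome SD of 1 at both visits, no dropout, and a correlation rho between baseline and follow-up of 0.5 to 0.9.

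**Step 1: what the sentence implies.** Assessing change within a group over time requires the baseline score to be a response in the model. Its mean can then be free in each arm or common to both. The article states no constraint, and the conventional model leaves the means free.

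**Step 2: equivalence.** A mixed model with group, time and group-by-time was fitted to one simulated two-visit data set (rho 0.7). The group-by-time coefficient was 0.4213 (SE 0.1497). The difference in mean change was also 0.4213 (SE 0.1497). In the same data a mixed model with a common baseline mean gave SE 0.137, and ANCOVA on baseline gave SE 0.130. The loss therefore comes from freeing the baseline means, not from using a mixed model.

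**Step 3: variances per participant.**

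- Change score: 1 + 1 − 2·rho = 2(1 − rho)
- Baseline-adjusted: 1 − rho²
- Ratio: (1 − rho²) / [2(1 − rho)] = (1 + rho)/2

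The SE of the contrast is √(variance × 2/48). The narrowing of the interval is 1 − √ratio. The number a change-score analysis would need to match 96 with adjustment is 96/ratio.

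| rho | SE, change | SE, adjusted | Variance ratio | Interval narrower by | Equivalent n |
|---|---|---|---|---|---|
| 0.5 | 0.204 | 0.177 | 0.75 | 13% | 128 |
| 0.7 | 0.158 | 0.146 | 0.85 | 8% | 113 |
| 0.8 | 0.129 | 0.122 | 0.90 | 5% | 107 |
| 0.9 | 0.091 | 0.089 | 0.95 | 2.5% | 101 |

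At rho 0.7 the 95% half-width falls from 1.96 × 0.158 = 0.31 SD to 1.96 × 0.146 = 0.29 SD. Within one country (12 per arm) the SE falls from 0.316 to 0.292 SD.

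**Step 4: simulation.** With 4,000 simulated trials per scenario and no variation between countries, the ratios were 0.756, 0.876, 0.914 and 0.951. These are close to the formula and slightly less favourable, since it ignores simulation error and the cost of estimating the baseline slope.

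**Step 5: country.** Adding country as a main effect to the conventional model in Step 2 left the result at 0.4213 (SE 0.1497), because a stable country effect cancels in the change. Adding it to ANCOVA multiplied the variance by 0.99 to 1.04 for assumed country intraclass correlations of 0, 0.1 and 0.2. That is essentially no gain.

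**The case against.** The strongest objection is that the article never specifies the model criticised here. It does not mention free baseline means or a change score. A mixed model with a common baseline mean is also a linear mixed model and fits the quoted sentence. A condensed article may leave such detail to a full protocol or analysis plan that is not shown. This stands in part: the point is conditional on the conventional reading, and the missing covariate list is not a finding. But the article does state its analysis target, and that wording leads most naturally to the less efficient contrast while putting within-group change alongside the randomised comparison.

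The second objection is size. The gain is 8% of interval width at rho 0.7 and 2.5% at rho 0.9, in a feasibility trial with no stated power. This stands too, and it limits the weight of the point.

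Three stronger readings are tempting but unsupported:

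- **That the planned estimate is biased or the sample size wrong.** The change contrast is unbiased under randomisation. Carrying chance imbalance into the estimate is the same variance penalty seen from another side. The sample size rests on a rule of thumb that the contrast does not affect.
- **That precision is lost because the pooled model names no country term**, given that "as the results may differ across countries, we consider each country an individual site for the feasibility RCT". Step 5 shows no such loss for stable country effects. Country could help only if the change itself differs by country, for which the article gives no figure. Nor is country ignored, since separate analyses are planned.
- **That disability score must be a covariate, or that the timing of baseline is a defect.** The article gives no figure for a gain from the former and does not state the order of baseline assessment and randomisation. Neither is claimed here.

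**Conclusion.** The point holds in conditional form, as an improvement that costs nothing and not as an error that invalidates a result. If the mixed model is fitted conventionally, its treatment contrast is the difference in mean change, and the baseline-adjusted contrast has (1 + rho)/2 of its variance. Over the assumed range of rho from 0.5 to 0.9, that is a variance reduction of 25% down to 5%.

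The figures assume 1:1 allocation, equal SDs at the two visits, complete data and a baseline score unaffected by allocation. The direction does not depend on equal SDs. With SDs s0 at baseline and s1 at follow-up, the change-score variance exceeds the adjusted variance by (s0 − rho·s1)², which is never negative. If the full analysis plan already fixes a common baseline mean or adjusts for baseline, the loss does not arise and only the article's wording needs clarifying.

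**What to change.** Add one sentence to Data Analysis and Statistical Plan. For 30STS and the other outcomes of research questions 3 and 4, the between-group effect is the post-intervention difference between arms adjusted for the baseline score, estimated from a mixed model with a common baseline mean or by ANCOVA. Within-arm changes are reported descriptively. Use the same contrast for the total group and for each country.

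Country may be included as a fixed effect in the pooled model to reflect the multicentre design, but should not be justified by an expected gain in precision.

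The cost is the sentence itself. No additional participants, visits or measurements are needed.

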### Ethical Considerations

Ethical approval has been obtained for WP2 from the Sheba Institutional Review Board (IRB; SMC-1154-24; May 1, 2024); the University of Limerick Education and Health Sciences Research Ethics Committee (2025_01_17_EHS; May 11, 2025); and the Central Denmark Region Committees on Health Research Ethics (1-10-72-140-24). Approval of the ethics application for WP3 is expected by September 2025. Ethics applications for the remaining WPs, including the multicenter feasibility RCT (WP4) and the economic evaluation (WP5), will be submitted to the appropriate IRB in each participating country prior to their initiation.

For WP2, all participants provide written informed consent prior to enrollment. The consent process includes comprehensive information on the study procedures, risks, benefits, and data confidentiality. All collected data are deidentified prior to analysis and securely stored in accordance with institutional data protection policies. Participants in WP2 do not receive financial compensation but may be reimbursed for travel expenses when applicable. Compensation for WP3 and future phases will be determined and approved through local IRB processes. No identifiable images or personal information will be included in the manuscript or any supplementary materials. If such materials are necessary for dissemination, explicit written consent will be obtained and submitted as required.

## Results

The PLATINUMS project received official funding in February 2024. Data collection for WP2 (the system usability and feasibility study) began in April 2025 across participating sites in Israel, Italy, Ireland, and Denmark. WP3 (validation of remote mobility measures) is scheduled to launch in September 2025, and the multicenter RCT (WP4) is planned to begin in January 2026. Project coordination and dissemination activities (WP7) have been ongoing since March 2025. Initial findings from WP2 are expected to be available by October 2025, with preliminary publications planned for mid-2026.

## Discussion

The PLATINUMS project aims to evaluate an innovative AI-based telerehabilitation system for people with MS, and if successful, it is expected to significantly advance the way rehabilitation is delivered to this population. The system is designed to provide accessible, individualized exercise programs with real-time feedback and therapist supervision, thereby overcoming some of the longstanding barriers to facility-based care. Through its structured, multiphase approach, the project will generate essential data on usability, feasibility, clinical validity of remote assessments, and preliminary efficacy of telerehabilitation interventions.

This protocol builds on a growing body of research demonstrating the potential of telerehabilitation to support physical function in people with MS while addressing several limitations observed in earlier studies. A recent scoping review identified two main categories of telerehabilitation interventions, exergaming and web-based physical therapy, both of which have shown promising results in improving gait and balance in people with MS [49]. For example, exergaming systems such as Microsoft Kinect–based virtual reality and home-based balance training tools led to significant improvements in ambulation speed, dynamic balance, and postural control [50,51]. Similarly, web-based physical therapy programs, including both those with real-time supervised and asynchronous formats, have demonstrated improvements in gait function and balance scores [52,53].

While previous interventions often lacked scalability or relied on specialized hardware, the PLATINUMS system leverages AI and widely available consumer devices, making it more practical for widespread use. The planned international feasibility trial further enhances the study’s relevance by including participants across diverse health care contexts, thereby increasing the potential for future implementation.

A particular strength of this study is its integration of technological innovation with a rigorous clinical and economic evaluation. By examining feasibility alongside psychometric testing and cost-effectiveness, the project will provide comprehensive insights into the practicality of scaling up such solutions in real-world settings. The inclusion of both patient-centered outcomes and system-level data will allow for a nuanced understanding of how AI-driven telerehabilitation can influence care delivery for people with MS. Still, as this is a protocol, all conclusions must remain provisional until data collection is complete. It will be important to interpret future findings with an understanding of the feasibility trial’s exploratory nature.

Several limitations and potential challenges should be acknowledged. First, as a feasibility study, the sample size may not be sufficient to detect small but clinically meaningful effects, and findings may not be generalizable beyond the populations and settings involved. Second, adherence to home-based interventions can be variable and difficult to monitor objectively outside controlled settings. To address this, we will incorporate remote use tracking, patient engagement strategies, and therapist follow-up. Third, technical issues such as hardware compatibility, internet connectivity, and user literacy may affect intervention delivery. These will be documented throughout the study and considered in the interpretation of results. Importantly, as with any AI-enabled solution, algorithm transparency, how well it can adapt to individual needs, and potential biases must be critically evaluated before broader deployment. Given that this is a feasibility protocol, any conclusions will remain provisional until the trial is completed and the data are evaluated.

Looking forward, the outcomes of this study are expected to inform the design of a fully powered RCT, as well as broader efforts to integrate digital health technologies into routine clinical practice. The knowledge generated may also prove relevant to other neurological conditions where mobility impairments are prevalent. A dedicated dissemination strategy has been developed to ensure that findings reach key stakeholders, including clinicians, patients, and health policy decision-makers. Ultimately, the PLATINUMS project seeks not only to assess a novel intervention but to lay the groundwork for a more accessible, personalized, and sustainable model of rehabilitation for people with MS.

## Appendix

Multimedia Appendix 1 SPIRIT (Standard Protocol Items: Recommendations for Interventional Trials) checklist.

Multimedia Appendix 2 Peer-review report from the funding agency (THCS Call Steering Committee; European Partnership on Transforming Health and Care Systems (THCS), Horizon Europe, European Union.

## Abbreviations

20SLS: 20-second single-leg stance
30STS: 30sec-sit-to-stand test
6MWT: 6-minute walk test
AI: artificial intelligence
EDSS: Expanded Disability Status Scale
FITT-VP: frequency, intensity, time, type, volume, and progression
FRT: functional reach test
IRB: institutional review board
MFIS: Modified Fatigue Impact Scale
MS: multiple sclerosis
MSIS-29: 29-item Multiple Sclerosis Impact Scale
MSWS-12: 12-item Multiple Sclerosis Walking Scale
PLATINUMS: Implementation of an Advanced Telerehabilitation Solution for People With Multiple Sclerosis
QIDS: Quick Inventory of Depression Symptomology
RCT: randomized controlled trial
RQ: research question
SDMT: Symbol Digit Modality Test
SPPB: Short Physical Performance Battery
STAI: State-Trait Anxiety Inventory
T25FWT: timed 25-foot walk test
TUG: timed up and go test
TUQ: Telehealth Usability Questionnaire
WP: working package
